**Fig. 2 Fig2:**
[figure not shown]
Fatigability protocol with handgrip and EMG acquisition. **a** Neuromuscular fatigability protocol: the green box represents the warm-up period, lasting a maximum of 1.5 min; the orange arrows are FSC; the blue lines are MVC and the purple lines are contractions at 40% of MVC. The red points represent the maximal forces awaited allowing critical force determination, while the evolution is represented with a red spotted line. Rest duration is 20 s (*), 2 min (nos. 1 and 2), 5 min (no. 3), 1 min (no. 4), 2 min (no. 5) and 3 min (no. 6). **b** Parallels between the 40% MVC contractions required and the muscle activation signals recorded. FSC: fast sub-maximum contraction; MVC: maximum voluntary contraction

#### Fatigue

The perception of fatigue is defined as a subjective sensation of weariness, increasing sense of effort, mismatch between expended and actual effort [4]. We will use two questionnaires to assess fatigue: the Functional Assessment of Chronic Illness Therapy-Fatigue (FACIT-F) and the Multidimensional Fatigue Inventory (MFI-20).

FACIT-F is a brief validated French-language questionnaire [39] consisting in 13 simple pragmatic statements (e.g., I am too tired to eat) accompanied by the Likert scale (0: “never or almost never” to 4: “always or almost always”). The final score ranges from 0 to 52, with an inverse relationship between the score and fatigue.

MFI-20 is also a validated French-language version of a widely-used questionnaire [40], focusing on fatigue. It is composed of statements covering self-perception, ranging from extremely positive (e.g., physically I feel/I am in excellent condition) to extremely negative (e.g., physically I feel/I am able to do very little). In the case of the MFI-20, there is a direct relationship between the patient’s score and perceived fatigue while exploring 4 topics: general fatigue, mental fatigue, reduced activity and motivation.

#### Anthropometric, clinical, nutritional and biochemical data

Relevant data will be collected from medical records. They will include age, body mass index, gender, presence of diabetes mellitus (defined as glycemia > 126 mg/dl while fasting or using oral hypoglycemic medications or insulin) and kidney disease (i.e., cause and creatinine, urea and proteinuria values), time of follow-up, Charlson Comorbidity Index (CCI) [41], Malnutrition Inflammation Score (MIS) [42], albumin, total cholesterol, high-density lipoprotein, low-density lipoprotein, triglycerides, uric acid, calcium, phosphorus, parathyroid-hormone, vitamin D, bicarbonate, sodium and potassium values. The most recent available data will be recorded within 3 months for CKD patients and 6 months for control volunteers.

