**Methods:**

This is a case-control, prospective, interventional study. Inclusion criteria: age ≥ 60 years; CKD Stage 3b-5; clinical stability (i.e. no hospitalization and ≤ 25% in creatinine increase in the previous 3 months). Controls with normal kidney function will be matched in terms of age, gender and diabetes mellitus (requisite: estimated glomerular filtration rate ≥ 60 ml/min/1.73m^2^ available in the last 6 months). Exclusion criteria for cases and controls: neuromuscular disease, life expectancy < 3 months.

The handgrip strength protocol is an intermittent test consisting in 6 series of 9 repetitions of 3-s sub-maximum contractions at 40% of the maximum voluntary contraction (MVC) and 2 s of resting time between contractions. Each series is separated by one fast sub-maximum contraction and one MVC. Strength is assessed with a high-frequency handgrip dynamometer paired with surface electromyography. Symptoms of fatigue are assessed using MFI-20 and FACIT-F questionnaires. In order to reach a statistical power of 96%, we plan to enroll 110 subjects in each group.

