In the course of chronic dialysis, the loss of muscle function is worsened by several factors, such as acidosis, loss of amino acids (up to 12 g per hemodialysis session or 4 to 6 g per day on peritoneal dialysis) and/or the presence of anorexia. In this context, the loss of strength is mainly attributable to a decrease in muscle-mass, characterized by the loss, or a decrease in size, of the contractile units [25–27]. Conversely, changes in the excitation-contraction coupling system have been little explored and are poorly understood, especially in patients with advanced CKD.

The grip isometric analysis (i.e., handgrip) is the most commonly used test to assess strength in patients who have advanced CKD [28]. The handgrip test is simple and rapidly performed; it yields reproducible results and can easily be integrated into routine clinical practice. In CKD patients, this test demonstrates a close correlation with survival, nutritional status and quality of life [29–33]. Moreover, an isometric contraction is less traumatic than a dynamic contraction [34]. Finally, a handgrip is a simple routine gesture and does not usually cause pain.

Thus, the aim of the study is to assess the neuromuscular features of elderly patients with advanced CKD and symptoms of fatigue coupled with dynapenia. To our knowledge, this is the first study to apply a complex set of validated tests to a large population of elderly patients who have advanced CKD but are not on dialysis, with respect to an age, sex and diabetes matched control group. The research will highlight neuromuscular features associated with dynapenia in elderly CKD patients. In addition, the relationship between dynapenia and subjective fatigue will be analyzed to identify novel therapeutic interventions. These findings will be rapidly translated into clinical practice, with a view to adapting physical activity programs to improve neuromuscular function in the management of CKD symptoms.

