### Setting of study

The study will be carried out in Le Mans hospital (France), in the outpatient unit for the care of advanced kidney disease (UIRAV, Unité pour l’Insuffisance Rénale chronique AVancée). The UIRAV unit follows about 210 patients which are not on dialysis (90% over the age of 60), whose mean age is 74 years; 60% are males and diabetes mellitus prevalence is approximately 50%. Of these, 180 patients are followed for CKD Stage 3b-5. As previously described by Fois et al. [35], UIRAV’s main objective is to offer frequent follow-up and to delay the start of dialysis. The frequency of controls is based on CKD stage and overall clinical stability. For example, patients with stable kidney disease Stage 3b are seen every 8 to 12 weeks, while patients with CKD Stage 5 are seen at least once a month. Study proceedings is described in Fig. 1.

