### Inclusion modalities

Participants will be informed about the study with a poster displayed in hospital or during medical consultations. Elderly CKD patients will be enrolled via the UIRAV unit. Control subjects will be enrolled through endocrinology, diabetology and dermatology units or during outpatient consultations with patients’ escorts.

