## Discussion

This study aims to quantify the prevalence of force decline in elderly patients affected by advanced CKD and to identify alterations at the level of the neuromuscular junction. The strength of this study is that it will be, to our knowledge, the first study to assess, in this “pre-dialysis” population, the prevalence of dynapenia coupled with an EMG recording to objectivate electromyographic fatigability features. It will also be the first trial combining an objective (i.e., F_crit_) and a subjective (i.e., FACIT-F and MFI-20) approach to assess fatigue in this population. The link between neuromuscular alterations and greater fatigue is in fact poorly understood [16], especially for CKD patients.

A higher prevalence of dynapenia is expected in the CKD population compared to the control group, with the highest prevalence in those with diabetes mellitus. Patients with diabetes appear to have decreased muscle functions [53, 54], but this result has been questioned [55]. We expect different neuromuscular features in CKD patients, specifically for F_crit_. CKD has been associated with difficulty in performing a standardized task but the origin of this disturbance (e.g., difficulty adapting the motor-unit discharge or difficulty recruiting the motor unit) is far less clear [48]. Our study will allow us to investigate these issues and clarify the underlying pathophysiological mechanisms. The temporal difference between the onset of the EMG signal and force production, i.e. the electromechanical delay, will be assessed during the FSC. We expect an increase in this delay, highlighting an alteration between the electrochemical process (i.e., synaptic transmission, propagation of the action potential, excitation-contraction coupling) and contractile and structural elements. A positive correlation is expected between subjective fatigue and objective fatigability.

The frailty of the elderly CKD population demands careful attention to the methodology employed, explaining the choice of this sub-maximum protocol to reduce as far as possible causing pain while inducing sufficient fatigue in this fragile population.

Better comprehension of the neuromuscular features of dynapenia and a deeper understanding of the relationship between fatigability and fatigue can help us guide interventions for elderly patients suffering from advanced CKD, with the final goal of targeting interventions to effectively improve quality of life and reduce morbidity.

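### The only diabetes definition, for a matching factor and covariate, misses known diabetics with fasting glycaemia at or below 126 mg/dl who take neither an oral drug nor insulin

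*Protocol article*

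**What the plan says.** The abstract states that "Controls with normal kidney function will be matched in terms of age, gender and diabetes mellitus", and the Background repeats the design ("with respect to an age, sex and diabetes matched control group"). The Statistical analysis section also lists diabetes among the variables for the logistic or multiple regressions.

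The only definition is in the section on anthropometric, clinical, nutritional and biochemical data: "defined as glycemia > 126 mg/dl while fasting or using oral hypoglycemic medications or insulin". The source is the patient file ("Relevant data will be collected from medical records"), with different look-back periods: "The most recent available data will be recorded within 3 months for CKD patients and 6 months for control volunteers". The cause of kidney disease is collected under the same heading but is not part of the diabetes rule. Glycated haemoglobin is asked for only in diabetic controls, as an inclusion criterion, and classifies nobody.

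The Setting section says of the unit that supplies the cases that "diabetes mellitus prevalence is approximately 50" per cent. The Discussion expects more dynapenia in CKD than in controls, "with the highest prevalence in those with diabetes mellitus".

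**The concern.** The rule has three routes to a diabetes code: a glucose value, an oral drug, or insulin. It has none for a diagnosis already in the file, and none for a non-insulin injectable. A known diabetic whose fasting glycaemia is at or below the threshold, and who takes neither an oral drug nor insulin, is therefore coded non-diabetic and would be matched to a non-diabetic partner.

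The gap is narrow. Diet-treated or untreated patients above 126 mg/dl are captured, as are injectable users who also take an oral drug or insulin.

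At stake is whether the groups are truly balanced on diabetes, and whether the diabetes term in the regressions and the comparison of diabetics with non-diabetics mean what they appear to mean. Adjusting for the same coded variable cannot remove an imbalance that the coding hides, and matching is hard to redo after enrolment.

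**Working it through.** **1. The plan's own figure.** The Statistical analysis section gives an 8% difference (±16%, read as the SD), 5% alpha and 110 per group for 96% power. Standardised difference = 8/16 = 0.5. Two-sided normal approximation: Φ(0.5 × √(110/2) − 1.96) = Φ(1.748) = 0.960. The figure reproduces and is not in dispute; the 8 points serve below as the yardstick.

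**2. Inputs for the hidden imbalance.**
- True diabetes prevalence in cases, π = 0.50 (Setting section, assuming enrolled cases resemble the unit).
- Assumed, because the document gives no figure: the share of true diabetics that the rule captures, s_c in cases and s_k in controls, 80% to 100%; true prevalence where controls are recruited, p = 20% or 50%; strength deficit due to diabetes, 4, 8 or 16 points; no non-diabetic coded as diabetic.

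**3. Formulas.** Coded prevalence in cases, reproduced in controls by matching: r = π·s_c. True diabetics hidden among coded non-diabetic controls: h = p(1 − s_k)/(1 − p·s_k). Imbalance = π − [r + (1 − r)h]. Bias = imbalance × deficit. A positive sign enlarges the apparent CKD deficit.

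Example with s_c = s_k = 0.9 and p = 0.2: r = 0.45; h = 0.02/0.82 = 0.0244; imbalance = 0.50 − (0.45 + 0.55 × 0.0244) = 0.037.

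| Captured, cases | Captured, controls | p | Imbalance (points) | Bias at deficit 4 / 8 / 16 (points) |
|---|---|---|---|---|
| 90% | 100% | 20% or 50% | +5.0 | 0.2 / 0.4 / 0.8 |
| 80% | 100% | 20% or 50% | +10.0 | 0.4 / 0.8 / 1.6 |
| 90% | 90% | 50% | 0 | 0 / 0 / 0 |
| 90% | 90% | 20% | +3.7 | 0.15 / 0.29 / 0.59 |
| 100% | 90% | 20% | −1.2 | −0.05 / −0.10 / −0.20 |
| 100% | 90% | 50% | −4.5 | −0.18 / −0.36 / −0.73 |
| 100% | 80% | 50% | −8.3 | −0.33 / −0.67 / −1.33 |

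**4. The diabetes comparison within cases.** 110 × 0.50 = 55 diabetic cases. At 90% captured, 5.5 are missed and the coded non-diabetic stratum is 110 − 49.5 = 60.5, of which 5.5/60.5 = 9.1% are diabetic. At 80% captured, the share is 11/66 = 16.7%. If missed diabetics resemble captured ones, the contrast between diabetics and non-diabetics shrinks to about 91% or 83% of its true size.

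**The case against.** The strongest reply is that this is a wording gap of little consequence. The primary objective, the prevalence of dynapenia in CKD patients, is judged against reference values by age and sex, so diabetes matching plays no part in it. The sample size is unaffected. The definition sits under data collection, and an article may leave the operational matching rule to the full protocol. All of that stands and limits the weight of the point. It does not remove it: this is the only rule given, and a rule that is stated can be judged as stated. If matching uses another rule, the matching factor and the covariate may differ, which also needs settling.

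Three stronger readings are tempting and are not supported.

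- A reader might infer that the missed diabetics are mostly CKD cases, for instance because glucose-lowering drugs have been stopped, so that weakness due to diabetes would be credited to CKD. The document says nothing of the kind and gives no rates. On recruitment it says "Control subjects will be enrolled through endocrinology, diabetology and dermatology units or during outpatient consultations with patients’ escorts", so controls too may include diabetics whom the rule misses. The table shows the sign reversing.
- A reader might take the request for glycated haemoglobin in diabetic controls only as part of the misclassification. It is unequal between the groups, but it misclassifies nobody, and no analysis by glycaemic control is described.
- A reader might say that the rule looks only at current treatment. The definition does not use that word; it is an inference from the 3- and 6-month windows.

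**Conclusion.** The point holds as a minor definitional flaw that is cheap to correct. Read literally, the rule misclassifies an identifiable type of known diabetic on a variable used for matching and for adjustment. The direction of any resulting imbalance cannot be known from the document. Across the assumed inputs, the bias runs from about −1.3 to +1.6 points on the planned 8-point difference. The upper end requires 20% of diabetics to be missed in cases, none in controls, and a diabetes deficit twice the planned CKD difference. With equal capture and equal prevalence in the two groups it is zero. The matched case-control contrast and the diabetes covariate or subgroup are affected. The primary prevalence estimate and the power calculation are not.

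**What to change.** Before matching, and identically for cases and controls, define diabetes as any one of: a recorded diagnosis (including diabetic kidney disease recorded as the cause of CKD); any glucose-lowering drug prescribed for diabetes; or fasting glycaemia above 126 mg/dl. State that this variable is the matching factor, and use the same variable in the regressions and in any diabetic subgroup.

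Optionally, record the latest glycated haemoglobin on file for diabetic cases, so that the item exists in both groups.

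The cost is one reworded definition and slightly more record review. It needs no new test or visit and leaves the sample size unchanged.

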### Inclusion criteria

#### Cases

Age ≥ 60Estimated glomerular filtration rate based on the Chronic Kidney Disease Epidemiology Collaboration (CKD-EPI) equation ≤45 ml/min/1.73m^2^ for at least 3 monthsStable clinical condition: no hospitalization; serum creatinine increased by a maximum of 25% in the previous 3 months

#### Controls

Age ≥ 60Available blood tests within 6 months showing normal renal function (estimated GFR > 60 ml/min/1.73m^2^) and glycated hemoglobin values for diabetic controlsStable clinical condition: no hospitalization in the previous 6 months

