## Methods

### Aims

The primary objective of this trial is to define the prevalence of dynapenia in elderly CKD Stage 3b-5 patients. This will be achieved through the analysis of handgrip strength.

The secondary objective is to define the characteristics of dynapenia in elderly patients with advanced CKD during a standardized task considering:
the evolution of MVC;the evolution of the discharge frequency of motor units;motor-unit recruitment ability;the evolution of the delay between the nervous stimulus and contraction;the relationship between dynapenia and subjective fatigue.

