### Definition and measures

#### Dynapenia

Dynapenia is an age-associated loss of muscle strength that is not caused by neurologic or muscle diseases [24]. In our study, dynapenia will be diagnosed if the mean of three MVC after a brief warm up, is lower than the reference value matched for age and sex. The study by Ramírez-Vélez et al. [36] will provide reference values for elderly patients.

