### Statistical analysis

Sample size calculation was based on the results of the handgrip strength test of Lin et al. [52], who analyzed a relatively large cohort of elderly patients suffering from CKD in 2019, and the handgrip strength reference values of Ramírez-Vélez et al. [36], who analyzed a larger population of elderly patients without CKD, stratified by age and sex. With an 8% (±16%) difference, accepting a 5% alpha risk, 96% statistical power will be reached by enrolling 110 CKD patients and 110 control subjects. Considering the number of patients followed in the UIRAV unit (i.e., approximately 180 older than 60), we should be able to enroll the participants within 1 year.

Signal filtering and analysis will be performed with Matlab 2018a v9.4 (The MathWorks Inc., Natick MA, USA) and statistical analysis will be performed with SPSS v14 (IBM Corp., Armonk NY, USA). Group comparison for normally distributed variables will be assessed by means of the analysis of variance (ANOVA) or the unpaired Student T-Test. For non-normally distributed variables the Kruskal-Wallis or the Mann-Whitney Test will be used. In addition, the chronological variables (e.g., evolution of the MVC during the test) will be analyzed by mixed models with fixed effect or ANOVA with repeated measures if the test prerequisites are satisfied (normality, homoscedasticity and sphericity).

Qualitative data will be compared with the Chi^2^ or the McNemar Test.

Correlation analyses will be performed with the Pearson Test. Logistic or multiple regressions will be performed to assess the effect of different variables on the outcomes: age, sex, body mass index, stage of renal disease, diabetes mellitus, MIS and CCI (either continuous or dichotomized) as well as biochemical data. A *p* < 0.05 will be considered statistically significant.

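### Controls must be hospital-free for 6 months but CKD cases for only 3, an unexplained one-sided health filter that probably widens the case-control differences slightly

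*Protocol article*

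**What the plan says.** The Protocol article sets the hospital-free period in four places:

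- **Inclusion criteria, Controls:** stability means "no hospitalization in the previous 6 months".
- **Inclusion criteria, Cases:** stability means no admission and a limited rise in creatinine, with 3 months closing the clause. The abstract confirms that the period covers both conditions: "no hospitalization and ≤ 25% in creatinine increase in the previous 3 months".
- **Exclusion criteria:** one list, not divided by group, bars anyone admitted in the 3 months before the test.
- **Abstract, Methods:** the exclusions are introduced as common to both groups: "Exclusion criteria for cases and controls: neuromuscular disease, life expectancy < 3 months".

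No reason is given for the longer control period. Three other parts of the article bear on the point. Matching is limited to three factors: "Controls with normal kidney function will be matched in terms of age, gender and diabetes mellitus". The look-back for recorded data also differs by group: "The most recent available data will be recorded within 3 months for CKD patients and 6 months for control volunteers". The regression covariates listed under Statistical analysis include comorbidity (CCI) and malnutrition-inflammation (MIS) scores, but not recent admission.

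**The concern.** In a case-control comparison, eligibility should be the same in both groups apart from the condition under study. Here one group passes a stricter recent-health filter than the other. The protocol itself treats admission as a sign of instability, and recent illness plausibly goes with lower strength and more fatigue, which are what the study measures. Removing recently admitted people from the control group alone makes the controls look fitter. That pushes the comparisons towards the results the Discussion expects, namely more dynapenia and different fatigability in CKD.

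The comparison with matched controls is the second aim in the abstract, and the sample size of 110 per group is built on it. A bias of this kind does not shrink as the sample grows.

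**Working it through.** **Step 1: which rule applies to whom.** A participant must meet every inclusion criterion and no exclusion criterion. Time since last admission then decides as follows:

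| Last admission | Case | Control |
|---|---|---|
| Within 3 months | not eligible | not eligible |
| 3 to 6 months ago | eligible | not eligible |
| More than 6 months ago, or never | eligible | eligible |

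Nobody receives two conflicting decisions. The groups differ only in the middle row.

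**Step 2: the plan's own figure.** Statistical analysis gives "With an 8% (±16%) difference", a 5% alpha and 110 per group. I read the ± figure as the SD and assume a two-sided test.

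- SE = 16 × √(2/110) = 2.157 points
- 8 / 2.157 = 3.708
- Power = Φ(3.708 − 1.960) = 0.960

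The stated 96% is reproduced (0.958 with the noncentral t). The admission window does not enter this calculation, so aligning the windows leaves the planned 110 per group and the power unchanged.

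**Step 3: size of the bias.** Let q be the share of otherwise eligible controls admitted 3-6 months ago, and g the number of points by which they are weaker than the other controls. Excluding them raises the control mean by q × g. The documents give neither q nor g. Both are assumptions: q = 2-10%, g = 4-20 points on the scale of the 8% difference.

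| q | g | Bias (points) | Share of 8 |
|---|---|---|---|
| 2% | 4 | 0.08 | 1% |
| 5% | 8 | 0.40 | 5% |
| 5% | 16 | 0.80 | 10% |
| 10% | 16 | 1.60 | 20% |
| 10% | 20 | 2.00 | 25% |

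**Step 4: effect on a test when the true difference is zero.** For a bias of b points the two-sided false-positive rate is 1 − Φ(1.960 − b/SE) + Φ(−1.960 − b/SE), with SE = 2.157.

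- b = 0.5: 5.6%
- b = 1.0: 7.5%
- b = 2.0: 15.3%

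**Step 5: what is not touched.** The primary objective concerns the cases alone: "The primary objective of this trial is to define the prevalence of dynapenia in elderly CKD Stage 3b-5 patients". A patient is classed as dynapenic if the mean MVC "is lower than the reference value matched for age and sex", and that reference comes from an external study. The control window cannot move this estimate. It can move the prevalence found among controls, and hence any comparison of prevalence between the groups.

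**The case against.** The strongest defence is that 6 months fits the rest of the control specification. Control blood tests may be up to 6 months old and control data are recorded over 6 months, against 3 months for CKD patients, who are seen far more often. In each group the hospital-free period equals the permitted age of the data. The article does not give this as its reason, but the pattern makes a deliberate choice plausible. It also exposes a cost of simply shortening the control window: a control with a five-month-old eGFR and an admission four months ago would qualify on a test taken before that admission. This point stands, but it argues for tying the blood test to the admission, not for unequal admission windows.

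The defence is also right that the size is wholly assumed. A share of 5-10% in one three-month period would mean, at a constant independent rate, 1 − 0.95⁴ = 19% to 1 − 0.90⁴ = 34% admitted per year. That is a lot for stable outpatients and patients' escorts. At 2% it is 1 − 0.98⁴ = 8%. The deficit must also persist 3-6 months after the admission.

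Three stronger readings are tempting and are not supported:

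- **That the criteria contradict each other.** The exclusion list does not admit a control hospitalized four months ago; it only fails to exclude that person. The inclusion rule then bars them. For controls the 3-month exclusion is redundant, not in conflict.
- **That the primary result is biased.** It rests on CKD patients and external reference values.
- **That no analysis can repair the imbalance.** If admission dates are known, cases can be restricted to those free of admission for 6 months, which puts both groups under the same rule. Adjustment for CCI and MIS may also carry part of the link between admission and strength.

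**Conclusion.** The concern holds as an unexplained inconsistency of low to moderate severity. Controls face a longer hospital-free requirement than cases, and neither the matching nor the listed covariates address it directly. The likely effect is a modest widening of the case-control differences in strength, fatigability and fatigue, in the direction the study expects. The direction rests on the judgement that recent admission goes with weaker grip and more fatigue; the documents do not state it. Under the assumed inputs the bias is about 1-25% of the planned 8% difference. The low end is more credible, because the upper end needs both a high admission rate and a large, lasting deficit.

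**What to change.** - **Eligibility.** Use one hospital-free window for both groups, or state why they differ. Three months for controls would agree with the abstract, the criterion for cases and the exclusion list. Add that a control's qualifying blood test must postdate any admission.
- **Data.** Record the date of last admission for every participant. It is not among the variables listed under Anthropometric, clinical, nutritional and biochemical data.
- **If enrolment has already begun under the unequal windows.** Add a sensitivity analysis of the case-control comparisons restricted to cases with no admission in the previous 6 months. The prevalence of dynapenia among CKD patients should still use all cases.

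**Cost.** A short amendment and one extra data field. A few controls may need a newer blood test. The restricted analysis is slightly smaller. As an illustration, if 10% of cases dropped out of it (an assumption), 99 cases against 110 controls give SE = 16 × √(1/99 + 1/110) = 2.217, and power for the planned difference is Φ(8/2.217 − 1.960) = 95%. The planned sample size does not change.
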